**Fig. 6 Fig6:**
[figure not shown]
BETTER WISE Project data collection timeline. EMR = patient chart abstraction (paper or electronic); HS = BETTER WISE health survey; PP = Prevention Practitioner visit

**Fig. 7 Fig7:**
[figure not shown]
BETTER WISE Project schedule of enrolment, interventions, and assessments

Before the visit, the PP will review the patient’s health survey responses and the medical chart to determine which prevention and screening actions the patient is eligible to receive and to prepare to discuss the patient’s risk for chronic diseases such as cancer, diabetes, and heart disease. Using shared decision-making and Brief Action Planning, the PP and the patient will develop a personalized prevention prescription. The prevention prescription, written on the standardized BETTER WISE form, may include plans for screening and referrals to programs (e.g., smoking cessation).

##### Wait-list control group

Wait-list control patients will be mailed: 1) the website link to the BETTER WISE health survey, and 2) the study consent form to completed and returned to the study team using a pre-addressed, stamped envelope. Wait-list control patients will be asked to complete the health survey immediately after agreeing to participate in the study and before their first visit with the PP, which will be scheduled upon completion of the intervention period of the study approximately 12 months later. Additional screening and prevention data will also be obtained for wait-list control patients by the PP or primary care clinic staff from the patient’s medical chart during the same data collection periods.

##### All patients

If access to a computer or the internet is identified as a potential barrier to participation, primary care sites may choose alternative methods (e.g. a paper survey) to enable patients to participate in the study.

#### Schedule of assessments and data collection

Prevention and screening data will be collected for the intervention group at six-month intervals to assess effectiveness of the intervention over 12 months and maintenance to 24 months and for secondary analysis. Each of the data collection points of the study are indicated in Figs. 6 and 7. Outcomes along with other pertinent covariate information will be retrieved from both the patient-completed BETTER WISE health surveys and patient medical records (electronic or paper).

##### The prevention and Cancer surveillance prescriptions

At the initial prevention visit, patients will be provided with a prevention prescription that summarizes their prevention and screening status, describes some goals for prevention, provides follow-up timelines, and lists any individualized screening recommendations. Prevention prescription copies will also be placed in patients’ medical records and will be used as a secondary data source. The prevention prescriptions will capture the information as outlined in Table 2.

**Table 2 Tab2:** Prevention Prescription Data

Description	Data to be Collected
All relevant chronic disease prevention and screening test results and values	cholesterol, fasting blood sugar, glycated hemoglobin, stool for blood, sigmoidoscopy, colonoscopy, pap, and mammogram
All relevant cancer surveillance results and values depending on personal history of cancer	breast - mammography, bone density; colorectal – colonoscopy, carcinoembryonic; antigen test, computerized axial tomography; prostate - prostate specific antigen test
Physical and vital information	blood pressure, weight, height, and body mass index For patients randomized to the intervention group, the PP will take the BP, weight and height measurements during the visit with the patient. For patients randomized to wait-list control, these will be collected from their medical record (electronic or paper) at baseline and 12-month data collection time points.
Referrals made or actions to be taken by the patient, PP, or primary care team in order to follow up on identified CCDPS items	Description of referrals and actions taken

##### The S.M.A.R.T. goals sheet

Along with the prevention prescription, patients will receive a copy of their S.M.A.R.T (specific, measurable, attainable, realistic, time-based) goals sheet. The prevention prescription informs the patient about their CCDPS status. After reviewing the patient’s CCDPS status, the PP will use shared decision-making and Brief Action Planning to help patients make S.M.A.R.T goals for their health. These will be documented on the S.M.A.R.T. goals sheet, as will the patient’s confidence in achieving each goal. Patients will be advised to make a maximum of three goals to ensure that achievement of each is feasible. Copies of the goals sheet will also be filed in patients’ medical records and used for secondary data analysis.

### Evaluation and impact of the intervention

#### Outcomes and statistical analysis

Outputs and outcomes include both practice- and patient-level outcomes (Fig. 8). To demonstrate the effectiveness of BETTER WISE, we will determine if cancer surveillance care and general prevention and screening outcomes improve for patients who receive an individualized visit with a PP, as determined by a composite index, when compared to wait-list controls at 12 months follow-up. The analysis will adhere to the intention-to-treat principle in that none of the enrolled patients will be excluded from analysis and all patients will be analyzed according to the randomization scheme (see Fig. 9). The unit of analysis will be the individual patient.

**Fig. 8 Fig8:**
[figure not shown]
BETTER WISE Project logic model. CCDPS = cancer and chronic disease prevention and screening

**Fig. 9 Fig9:**
[figure not shown]
BETTER WISE Project CONSORT flow diagram

##### Sample size calculations

Based on the findings from our previous research (BETTER trial and BETTER 2 study), we estimate the intra-class correlation coefficient (ICC) to be 0.30. From the BETTER trial, we anticipate the percentage of achieved CCDPS actions in the wait-list control arm will be approximately 20%. To detect a 20% intervention effect (i.e., the proportion of achieved CCDPS actions for patients randomized to the BETTER WISE intervention is 40%, compared to 20% for wait-list control) with 80% power, we will need to recruit approximately four patients per physician to achieve our sample size requirements per area of interest (cancer survivors and general population patients) at 5% alpha. The 20% intervention effect size is conservative given information gathered from the BETTER trial. As such, we would require four cancer survivors and four general population patients for each participating physician to have sufficient power to conduct sub-group analyses (i.e. measuring the effectiveness of the PP intervention in cancer survivors and the general population patients).

We will also target patients with complex medical needs as described by the province of Alberta’s billing definition of complex needs. In the BETTER trial, 25% of patients 40 to 65 years of age met the Alberta’s billing criteria for complex needs. To guarantee that we will recruit enough patients to meet the definition of complexity, we will increase our total sample size to 16 patients (four cancer survivors and 12 general population patients) for a total of four patients with complex needs (i.e., 25% of 16 = 4). This will allow sufficient power to conduct sub-group analyses with respect to measuring the effectiveness of the PP intervention on patients with complex needs.

To account for possible study withdrawal and/or loss to follow-up, we will further inflate our sample size by 25% for a total of 20 patients per physician (five cancer survivors and 15 general population patients) for a total sample size of 1280 patients (320 cancer survivors and 960 general population patients). A total of 30 patients per physician will be recruited to participate in the project to ensure our target sample size of 20 patients per physician is met. Participating practices may choose to over-sample cancer survivors or patients who meet the definition of complex needs in order to reach their target sample (five cancer survivors and 15 general population patients).

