**Fig. 2 Fig2:**
[figure not shown]
BETTER WISE Project design schema for practices in Ontario and Newfoundland & Labrador

All eligible breast, colorectal, and/or prostate cancer survivors will be invited; the remainder of the sample will be designated as general population patients, which will include patients with complex needs. We plan to recruit 20 patients per physician (five cancer survivors and 15 general population patients), with priority given to cancer survivors.

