#### Identifying the general population patient sample

The PPs and/or primary care clinic staff working with the research team will identify eligible patients from the remaining pool. To select patients in the non-cancer survivor sample, the study biostatistician will generate a random number sequence. Patients will be invited to participate in the order of the random number sequence and assigned a unique study identification (ID) number.

Standardized invitation letters will be signed by the PP and physician. As stated in the letter, the participating primary care site will call the patient five business days after mailing the invitation to determine if they are interested in participating. If the patient meets the inclusion criteria, a verbal consent process will be completed.

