**Fig. 10 Fig10:**
[figure not shown]
BETTER WISE Project timeline

Phase 2 of the project includes the pragmatic two-arm cluster RCT. The significant milestones are: 1) ethics approval obtained; 2) physicians and practices recruited, physicians randomized for RCT; 3) clinicians identified to take on role of PP and trained; 4) patients recruited; 5) completed PP visits with intervention and waitlist control patients.

Phase 3 of the project is the evaluation of impact.

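### Practices may over-sample complex-needs patients at their own discretion after physicians are allocated, with no rule that the choice be equal across arms or randomly drawn

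*Protocol article*

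**What the plan says.** Four parts of the protocol article bear on this.

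- **Who is in the group.** Setting, recruitment, and sample: "All eligible breast, colorectal, and/or prostate cancer survivors will be invited", and "the remainder of the sample will be designated as general population patients, which will include patients with complex needs". Each physician is to contribute five survivors and 15 general-population patients.
- **How they are chosen.** The section on identifying general-population patients names those who draw up the list: "The PPs and/or primary care clinic staff working with the research team will identify eligible patients from the remaining pool". The study biostatistician generates a random number sequence, and "Patients will be invited to participate in the order of the random number sequence".
- **The exception.** Sample size calculations, last paragraph: "Participating practices may choose to over-sample cancer survivors or patients who meet the definition of complex needs". The stated purpose is to fill the quotas of five and 15 above. The same section plans for four complex-needs patients per physician, to support a subgroup analysis.
- **The order of events.** Timeline lists the milestones as "physicians and practices recruited, physicians randomized for RCT; 3) clinicians identified to take on role of PP and trained; 4) patients recruited".

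The Randomization section makes the physician the unit of allocation and places physicians of both arms within a site.

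**The concern.** When clusters are allocated first and patients enrolled afterwards, randomization of physicians does not by itself protect against choosing different kinds of patients in the two arms. For the general-population group, the safeguard that the article states is the random-order invitation. The over-sampling sentence lets practices depart from it and does not say how the two rules fit together.

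Allocation is by physician, so anyone who knows a physician's arm knows the arm of each patient on that physician's list. The PP, who may be drawing up the list, also delivers the intervention.

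The primary outcome is the percentage of eligible actions that are met. Complex-needs patients may differ in which actions they are eligible for, how often they attend and how readily actions are met. An unequal complex share could therefore move the overall contrast and the general-population contrast, both of which the article plans to estimate. It could also affect the complex-needs sub-analysis: if complex patients were picked by staff in one arm and drawn at random in the other, they would not be comparable even within the subgroup.

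**Working it through.** **The plan's own figures.** These reproduce:
- 25% of 16 = 4 complex-needs patients per physician.
- 16 x 1.25 = 20 patients per physician.
- 20 x 64 = 1280 in total, with 5 x 64 = 320 survivors and 15 x 64 = 960 general-population patients.

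The point made here changes none of them. At 20 per physician, the plan's 25% gives an expected 0.25 x 20 = 5 complex-needs patients without any over-sampling, if that share applies to all its patients.

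**The rules side by side.**
1. Survivors: all eligible ones are invited, so over-sampling them overrides no random order. The issue is confined to complex-needs patients.
2. Complex-needs patients sit in the general-population group, which is invited in random order. Giving them preference means either leaving that order or using a separate random draw. The article mentions no separate draw.
3. Physicians are randomized at milestone 2 and patients recruited at milestone 4. The article does not say when a practice decides to over-sample, but selection of patients comes after allocation.
4. No text requires the option to be used equally for intervention and control physicians.

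**Size, for illustration.** If complex and other patients differ in the index by *d* points, and the complex shares of the general-population sample are *p1* and *p0* in the two arms, then:

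shift in the general-population contrast = (p1 - p0) x d

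shift in the overall contrast = 0.75 x (p1 - p0) x d, because 15 of 20 patients are general population.

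The article gives p0 = 25% and the 0.75. The values of p1 and d are assumptions; the documents contain neither.

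| p1 | d | General-population shift | Overall shift |
|---|---|---|---|
| 40% | 5 | 0.15 x 5 = 0.75 | 0.6 |
| 60% | 5 | 0.35 x 5 = 1.75 | 1.3 |
| 40% | 10 | 0.15 x 10 = 1.5 | 1.1 |
| 60% | 10 | 0.35 x 10 = 3.5 | 2.6 |

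The sign can go either way, since *d* may be positive or negative and either arm may be the enriched one. If both arms are enriched equally, p1 = p0 and the shift is zero.

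Against the planned effect of 40% versus 20%, the overall shift at d = 10 is 1.1/20 to 2.6/20, or about 6% to 13% of the target. The formula does not cover hand-picking within the complex-needs subgroup, whose effect cannot be sized from the documents.

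**The case against.** There is a good case that the danger is limited, and much of it stands.

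- **The choice belongs to the practice.** With 64 physicians in 16 practices there are on average four physicians each, and sites hold both arms. A practice that used the option uniformly would enrich both arms and cause no imbalance. This stands, but nothing in the text requires uniform use.
- **Motive.** A reader might infer that staff have a reason to favour complex patients for intervention physicians and none for control physicians. The article does not support that. Under Wait-list control group, control patients get their own PP visit about 12 months later, so any such reason is delayed rather than absent.
- **Compatibility.** A reader might also infer that over-sampling and random-order invitation cannot both be followed. That is too strong: complex patients could be drawn in random order from their own list. The gap is that the article does not say this is how it will be done. A fuller protocol might add the procedure, but the published sentence grants the discretion without condition.
- **Purpose.** The option could look unnecessary, since the five and 15 quotas do not depend on complexity. But the same section wants four complex-needs patients per physician, and an expected five does not secure four for each one. Deleting the option outright would ignore that aim.
- **Generalizability.** The rationale for the pragmatic design rests on minimal selection criteria, existing practices and tailoring, not on a random sample of patients. The point should not be argued from there.

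**Conclusion.** The point holds as an avoidable risk in the recruitment rules. The article expressly permits discretionary enrichment of complex-needs patients after allocation, by people who can know the arm, in a group otherwise protected by random-order invitation, and it sets no condition of equality or random drawing.

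It does not show that one arm will be enriched and the other not. That stronger reading needs practices to treat their own intervention and control physicians differently, which the text allows but does not state.

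On the assumed 10-point index difference, with a 40-60% complex share throughout one arm against 25% in the other, the shift is 1.5-3.5 points in the general-population stratum and about 1.1-2.6 points overall, direction unknown. Those shares suppose that a whole arm is enriched, so a partial or mixed use of the option would give less. The result would not overturn a 20-point effect. It matters more for a smaller observed effect and for the comparability of arms in the general-population and complex-needs analyses. A change before recruitment is worth making because it is cheap and the selection cannot be undone later.

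**What to change.** Replace the discretionary sentence on complex-needs patients with one rule that applies identically to every physician in both arms. State the number of complex-needs and other general-population places per physician. For each physician, have complexity flagged on the full list of eligible patients, and have the biostatistician put the complex and non-complex lists in random order before the allocation is released to the practice. Staff then invite strictly in those orders until each quota is filled. The sentence can keep its reference to cancer survivors, since all eligible ones are invited in any case.

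This keeps the aim of four complex-needs patients per physician and leaves the total of 1280 unchanged. The cost is a short edit to the recruitment text and the work of flagging complexity when the list is drawn, together with holding back the allocation until the lists are fixed.

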#### Primary outcome and analysis

Effectiveness of the PP intervention will be assessed via a comparison of the composite outcome between intervention and control groups at 12-months. The primary outcome and performance indicator will be a composite index [19] of evidence-based chronic disease prevention and screening actions related to diabetes, heart disease, cancer screening, lifestyle factors associated with those chronic diseases and, for cancer patients, appropriate cancer follow-up care calculated at 12 months. The BETTER WISE composite index will be identical to the BETTER trial index in its mathematical definition, but items in the index may differ. The composite index is calculated as the total number of CCDPS actions met divided by the total number of CCDPS actions the patient is eligible to receive, multiplied by 100. The composite index is treated as a continuous outcome, expressed as a percentage that ranges from 0 to 100 and calculated at the patient level. A composite outcome will be used because it is not feasible to power the study to assess each individual item (multiple comparisons). We will revise the index content developed for CCDPS and adapted from the BETTER trial [10, 24] to reflect the CCDPS messages and actions recommended in each participating province to be consistent with jurisdiction-specific messaging.

We will examine the distribution of composite outcome for normality and will use proper transformation, if needed. Descriptive statistics (mean, standard deviation, median, quartiles for continuous variables, composite index) and counts/percentages for categorical variables (gender, level of education, etc.) will be used to describe the sample. The outcome measures and their components will be summarized at baseline and the end of the study using appropriate summary statistics for each physician, primary care practice, province, and overall. Generalized Estimation Equation (GEE) methods will be used for assessing the impact of interventions on prevention and screening of cancer and other chronic diseases in primary care. The GEE methodology provides a powerful method of analyzing correlated (clustered) data. We will estimate the intervention effect on the composite index and on the sub-components for the overall sample, and in the cancer and general population strata, respectively.

#### Secondary outcomes

Secondary outcomes will include 1) proportion of patients meeting the evidence-based targets, as measured by tracking specific CCDPS actions (e.g. mammograms completed) longitudinally at six, 12, 18 and 24 months, 2) number of targeted CCDPS actions that patients randomized to the intervention group were deemed eligible to undertake at baseline that are met (according to pre-defined targets) at 24-month follow-up, 3) a 24-month composite index score considering the number of targeted CCDPS actions patients were deemed eligible to improve at baseline, and 4) sub-analyses for the primary and secondary outcomes performed for cancer survivors and complex needs patients, where sample size permits.

#### Economic assessment

We will perform an economic evaluation of the intervention from the perspective of the health care payer, taking into account program costs and costs incurred by the recommended actions. We will estimate program costs in two ways: 1) by assuming that costs associated with the intervention are borne by the system directly and 2) by assuming that costs are absorbed via physician billings.

#### Evaluation of implementation

A qualitative evaluation will focus on the perspectives of patients, health care providers (including physicians and PPs), and other community members involved in the project. The purpose of the qualitative evaluation is to understand the impact of the approach as well as the implementation of the approach (e.g., impact on patients and practices including perceived benefits and disadvantages), and the uptake process (e.g., perceived barriers and enablers) including sustainability in different primary care contexts.

After the review of numerous implementation frameworks [24, 28–30], two frameworks were consistent with the study objectives [24, 28, 29]: 1) the ADKAR (Awareness, Desire, Knowledge, Ability and Reinforcement) [29] model will inform the qualitative evaluation on a micro level (individuals and individual practices) and 2) the CFIR (Consolidated Framework for Implementation Research) [28] model that will help us to understand implementation on a meso and macro level (i.e., overall picture, policy level). The qualitative component will complement Phase 2 by assisting with: 1) implementing our RCT in the practice setting and identifying early facilitators and barriers and 2) a deeper understanding of the practice context to help interpret our quantitative findings. Initial and follow-up focus groups and interviews of key informants (e.g., PPs, administrative staff, clinicians, allied health professionals) will be analyzed with constant-comparative methods [24]. All focus group and key informant interview participants will provide voluntary, written informed consent before participating.

Because participation outside of the prevention visit was challenging for patients in the original BETTER trial, we will invite patients to fill out a short feedback form following their appointment rather than inviting them to participate in a qualitative interview or focus group. In the previous implementation of BETTER [24], we found that a simple open-ended survey provided valuable responses from over 50% (*n* = 91/154) of patients. The survey asked three open-ended questions: 1) what patients liked about their visit, 2) what they would have liked to be different about their visit, and 3) other comments. For BETTER WISE, we expanded the patient survey by including the ASK-MI (Alberta Shared Decision Making Measurement Instrument) to gather more information about the prevention visit, specifically the level of shared decision-making between patient and PP dyads. The ASK-MI tool contains six Likert scale items and matches patients’ experiences of their prevention visit with PP’s responses of the same visit (e.g., to what extend the PP and the patient worked together to agree on a plan and the main concerns of the visit). BETTER WISE data captured by patient feedback surveys will be analyzed quantitatively using descriptive statistics and qualitatively using thematic content analysis.

